**Results:**

The data will be analysed on an Intention-To-Treat principle (ITT). Ethical approval was obtained from RTPO in September of 2023. Trial registration number: NL84446.099.23 METCnumber UMCG25.327. Outcomes will be published in peer reviewed journals and presented at (inter)national conferences.

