### Study interventions

2.3

Participants randomized to the surgical arm will undergo TORS with BOT reduction, a technique established by Vicini et al. in 2010 [13]. In the Netherlands it is an accepted and well tolerated technique to reduce the BOT [14]. Procedures will be performed under general anaesthesia by two head and neck surgeons of the Frisius Medisch Centrum Leeuwarden, following standardized protocols. Postoperative care includes a short clinical stay of 3 days and a clinical follow-up visit at 6 weeks.

Participants randomized to the control arm will receive non-surgical therapy, consisting of the gold standard treatment, CPAP or MAD, as determined by shared decision-making between patient and their physician. CPAP devices (Airsense 10 AutoSet, Airsense 10 Elite, Airsense 11 Autoset or Airsense 11 Elite) will be prescribed by the pulmonologists of the Frisius Medisch Centrum Leeuwarden and will be tailored to patient needs. CPAP devices will be fabricated by ResMed. Adherence data will be remotely monitored.

Participants receiving MAD will be evaluated by a maxillofacial oral surgeon and fitted with custom adjustable devices manufactured by SomnoMed, SomnoDent Flex. The MAD will be made in the dental laboratory of the Frisius Medisch Centrum Leeuwarden.

CPAP and MAD users will receive standardized counseling regarding usage, side effects, and expectations. Technical or adherence issues will be addressed through telephone follow-up and in-person visits as needed.

The following interventions are prohibited during the trial period [1]: use of CPAP or MAD after intervention via TORS [2]; other concomitant transoral surgery such as (bi maxillary) osteotomy [3]; other concomitant OSA treatment such as position therapy, hypoglossal nerve stimulation, nasal resistors, oropharyngeal exercises.

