### Study outcomes

2.5

The primary endpoint of this study is the mean AHI measured 6 months post-intervention. This time point was selected because it reflects the earliest clinically relevant assessment at which treatment effects are expected to be stable in both arms: after postoperative recovery following TORS and after establishment of CPAP/MAD use and adherence. The PG will be performed at baseline, 6 months and 12 months. A lower AHI reflects improved airway patency and is thus clinically meaningful in assessing treatment effectiveness between groups. Twelve month follow up is included as an important secondary endpoint to evaluate durability of treatment effects in this chronic condition. Secondary outcomes include: (1) 50% reduction of AHI at 6 months compared to baseline and or AHI below 20/h (Sher's criteria) [2,21] reduction of AHI at 12 months to <5/h will be defined as surgical cure [3,22] differences in mean ODI 4% values at 6 months and 12 months, and reduction of ODI 4% to 25% relative to baseline will be defined as clinically relevant [4,22] differences between FOSQ-35 [15] scores at 3 months, 6 months and 12 months in which an increase of 10% of the score compared to baseline on the FOSQ-35 questionnaire will be defined as clinically relevant [5,22] differences between scores of ESS at 3 months, 6 months and 12 months and a reduction on the ESS to <10 will be defined as clinically relevant [6,23] differences between scores of quality of life questionnaires EQ-5D-5L [19] at 3 months, 6 months and 12 months [7]; differences in scores on the visual analogue scales (VAS) for snoring, tiredness and globus in all patients between baseline, 3, 6 and 12 months [8]; VAS scores swallowing and taste for patients in the TORS group at baseline compared to 3 months, 6 months and 12 months.

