### Sample size calculation

2.8

To answer our primary objective 25 patients per arm must be included in the study. This sample size calculation is based on results of an earlier RCT where OSA surgery was compared to conventional therapy (medical management) [26]. At 6 months MacKay et al. found the means of AHI to be in group 1, the conventional group 34.5 with a standard deviation of 23.0 and in group 2, the surgery group 20.8 with a standard deviation of 18.4. We have chosen to select a smaller standard deviation compared to the literature, as retrospective analysis of our database of OSA patients treated with TORS show a mean of AHI at 3 months (n = 31) of 16.4 with a standard deviation of 12.0 and a mean of AHI at 1 year (n = 14) of 10.8 with a standard deviation of 8.48. As our inclusion and exclusion criteria are strict and like our retrospective data and we expect a similar outcome. Given the sample size, analyses will primarily focus on estimating treatment effects with 95% confidence intervals. Secondary outcomes and subgroup analyses will be considered exploratory. Group sample sizes of 21 and 21 achieve 82% power to detect a difference of 10.0 between the null hypothesis that both group means are 34.0 and the alternative hypothesis that the mean of group 2 is 24.0 with estimated group standard deviations of 10.0 and 12.0 and with a significance level (alpha) of 0.05 using a two-sided two-sample *t*-test. The detectable differences are estimated to be of clinical relevance. To correct for possible missing data, we calculated a 20% bigger sample size which results in a sample size of 25 patients per arm.

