### Statistical analysis

2.10

All statistical analyses will be conducted using IBM SPSS Statistics. The full analysis set (FAS) follows the Intention-To-Treat (ITT) principle and includes all planned subjects, except those with major protocol violations, no post-baseline data, or no study intervention.

Baseline characteristics, including age, gender, BMI, PG, ENT exam, DISE results, smoking, and reflux history, will be summarized using descriptive statistics. Quantitative variables will be presented as mean and standard deviation or as median with interquartile range or minimum/maximum, and qualitative data as frequencies and percentages, with 95% confidence intervals where applicable. Data normality will be assessed graphically and numerically. No formal statistical tests will be performed for baseline comparisons. The primary outcome (AHI at 6 months) will be analysed using independent *t*-test or Mann-Whitney *U* test depending on data distribution. Given the RCT design, adjustments for baseline differences are not foreseen. In case of missing data this will be mentioned in the results. Missing data will not be replaced. For all hypothesis testing, a two-sided p-value of less than 0.05 indicates statistical significance. Secondary outcomes will follow the same approach. For continuous variables, appropriate group comparisons (*t*-test, Mann–Whitney U, ANOVA, or Kruskal–Wallis) will be used. For categorical outcomes, Fisher's exact or Chi-square tests will be applied as applicable. Because the control arm includes two standard non-surgical modalities (CPAP and MAD), additional prespecified analyses will be performed to assess robustness. These include [1] subgroup analyses comparing TORS vs CPAP and TORS vs MAD separately (exploratory due to sample size) and [2] sensitivity analyses adjusting for control modality (CPAP vs MAD) when evaluating the primary endpoint. Treatment adherence data will be reported descriptively and considered when interpreting outcomes. Other study parameters will be analysed descriptively as outlined above.

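### The full analysis set is called ITT but drops major protocol violations and untreated patients, so a TORS patient who starts CPAP or MAD may be removed

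*Protocol article*

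**What the plan says.** The abstract (Results) states: "The data will be analysed on an Intention-To-Treat principle (ITT"). Section 2.10 says that the full analysis set follows that principle, but then that it "includes all planned subjects, except those with major protocol violations, no post-baseline data, or no study intervention". The same section says "Missing data will not be replaced" and that secondary outcomes are handled like the primary one. The article names no other analysis set.

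The first intervention that section 2.3 prohibits during the trial period is "use of CPAP or MAD after intervention via TORS".

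Section 2.5 makes mean AHI at 6 months the primary endpoint. Of the later visit it says: "Twelve month follow up is included as an important secondary endpoint to evaluate durability of treatment effects in this chronic condition". It also gives a responder definition for that visit: "reduction of AHI at 12 months to <5/h will be defined as surgical cure". Nothing there says whether the patient must be off CPAP or MAD when AHI is measured.

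**The concern.** An ITT set keeps randomised patients in their allocated arm whatever happens afterwards. A set that removes patients for violations after randomisation, or for not receiving the intervention, is not ITT, so section 2.10 contradicts its own label and the abstract.

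The violations clause matters most in the TORS arm. A TORS patient would start CPAP or MAD mainly because surgery left residual OSA, often once the 6-month PG has shown it. That act is expressly prohibited, so it could be classed as a major violation. The trial is open-label, so the classification could be made with the 6-month result known. The patients removed would be surgical failures, and those left would look better than the arm as randomised. The 12-month durability analysis is the most exposed, but the same set governs the 6-month primary analysis, which is affected if a device is started before that PG.

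The clause on patients without study intervention can act in either arm, and its direction is open.

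**Working it through.** **The plan's own figure.** Section 2.8 states 82% power with 21 per arm, a difference of 10.0, and SDs of 10.0 and 12.0. The noncentrality is 10 / sqrt((10² + 12²)/21) = 2.93. With 40 degrees of freedom and two-sided alpha 0.05 the power is 81.7%, so the figure reproduces. It does not bear on the exclusion rule, for which the plan gives no figure.

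**Inputs.** From section 2.8, the site's TORS database has "a mean of AHI at 1 year (n = 14) of 10.8 with a standard deviation of 8.48". These are assumptions, not in the article:
- the same mean and SD at month 6;
- a lognormal shape;
- a correlation of 0.7 between months 6 and 12;
- a share u of patients with month-6 AHI of 15 or more who start a device, varied from 5 to 50%.

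**Step 1, distribution.** σ² = ln(1 + (8.48/10.8)²) = 0.480, so σ = 0.693. μ = ln(10.8) − 0.240 = 2.139.
- P(AHI ≥ 15) = 1 − Φ((ln 15 − 2.139)/0.693) = 1 − Φ(0.821) = 20.6%.
- P(AHI < 5) = Φ((ln 5 − 2.139)/0.693) = 22.2%. This is the off-device cure rate.

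**Step 2, patients affected.** The affected fraction is a = 0.206u, and the chance of at least one in 25 is 1 − (1 − a)^25.

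**Step 3, effect of dropping them.** Patients with month-6 AHI of 15 or more have an off-device month-12 mean of 10.8 × Φ(0.7 × 0.693 − 0.821)/0.206 = 19.3. By simulation (2,000,000 draws), about 1.2% of them are below 5/h at month 12.
- Mean AHI if dropped = (10.8 − 19.3a)/(1 − a).
- Cure if dropped = (0.222 − 0.012a)/(1 − a).

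**Step 4, effect of keeping them with an on-device PG.** Assume on-device AHI is normal with mean 5 and SD 4, cut at 0, which has mean 5.2. Mean AHI = 10.8 − a(19.3 − 5.2).

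**Step 5, last PG before the device.** The month-6 mean of these patients is 10.8 × Φ(0.693 − 0.821)/0.206 = 23.5. Mean AHI = 10.8 + a(23.5 − 19.3).

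| u | Affected of 25 | P(at least one) | Cure if dropped | Mean if dropped | Mean if kept, on device | Mean, last PG before device |
|---|---|---|---|---|---|---|
| 5% | 0.3 | 23% | 22.4% | 10.7 | 10.7 | 10.8 |
| 10% | 0.5 | 41% | 22.7% | 10.6 | 10.5 | 10.9 |
| 25% | 1.3 | 73% | 23.4% | 10.3 | 10.1 | 11.0 |
| 50% | 2.6 | 93% | 24.6% | 9.8 | 9.3 | 11.2 |

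The off-device reference is cure 22.2% and mean 10.8.

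**Step 6, scale.** With 25 per arm the standard error of the difference is sqrt(8.48² + s²)/5. It is 1.9, 2.4 and 2.9 for an assumed control SD s of 4, 8.48 and 12. The largest shift in the table from dropping is 10.8 − 9.8 = 1.0.

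**Sensitivity.** With correlation 0.5 to 0.9 and u of 25 to 50%, cure if dropped stays at 23 to 25%. If month 6 still looks like the site's 3-month data (16.4, SD 12.0), 42% of patients are at 15 or more, and cure if dropped is 24 to 27% for the same u.

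**The case against.** The strongest reply is that the harm is conditional and small. The article does not define a major violation, a fuller document may do so, and secondary outcomes are declared exploratory. All of that stands, and it limits the severity. It does not remove the contradiction: the article itself fixes the exclusion and attaches the ITT label to it.

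A second reply is that keeping device users flatters TORS as well. For mean AHI this is correct. An on-device PG lowers the TORS mean further than dropping the patient would (10.1 to 9.3 against 10.3 to 9.8 at 25 to 50% uptake). The mean with these patients kept must therefore be described as a treatment-policy estimate, not as durability of surgery.

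Three stronger readings are tempting, and the article does not support them.
- A reader might infer that at least one affected patient is probable. That follows only from an assumed uptake of 25% or more in the main case. At 5 or 10% the chance is 23 or 41%, and the article gives no rescue rate.
- A reader might infer that section 2.3 equally bars a control patient from crossing to TORS. The item reads "other concomitant transoral surgery such as (bi maxillary) osteotomy". It concerns surgery other than TORS and does not name later TORS in a control patient.
- A reader might infer a serious inflation of the primary type I error. Removing the one to five worst of 25 TORS patients under no difference (both means 34, SDs 10 and 12) would raise it from 5% to about 7 to 29%. That assumes the worst possible selection and device starts before month 6, neither of which the article states.

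**Conclusion.** Wrong as written, and minor. Section 2.10 calls ITT a set that excludes patients for violations after randomisation and for not receiving the intervention, which contradicts the abstract. Combined with the device prohibition in section 2.3, this allows outcome-dependent removal of TORS failures. Removal is possible rather than certain. It mainly concerns month 12, and also the 6-month primary endpoint if a device starts before then.

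The size cannot be known from the article. Under the stated assumptions, with uptake of 5 to 50%, dropping these patients moves 12-month cure by at most about 2.4 percentage points (0.6 of a patient in 25). It lowers mean TORS AHI by 0.1 to 1.0 events/h, below the smallest standard error considered (1.9). The case for change is that a plan labelled ITT should not leave room for exclusions decided after the result is known.

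**What to change.** **Section 2.10.** Analyse all randomised patients with data in their allocated arm. Make no exclusion for violations after randomisation or for not receiving the intervention. Move those exclusions to a per-protocol sensitivity analysis.

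**Section 2.5.** Define surgical cure as a 12-month AHI below 5/h in a TORS patient not using CPAP or MAD. For the AHI responder outcomes, count a TORS patient who has started a device by that visit as a non-responder. In the main case this leaves cure at 22%.

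**Mean AHI.** Record the OSA treatment in use at each PG. Describe the mean with device users kept as a treatment-policy estimate. Add a sensitivity analysis that uses the last PG before the device was started.

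**Cost.** The change needs new wording and one case-report-form field. Clinical management does not change. The TORS response rate may look slightly less favourable. The treatment-policy mean may look better than surgery alone would give, which the report has to say. The last-PG analysis leans the other way, overstating the TORS mean by about 0.2 to 0.4 events/h at 25 to 50% uptake because of regression to the mean. The change is best made before any 6-month result is known.

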### Eligibility criteria

2.2

All patients presented at the otorhinolaryngology department of the Frisius Medical Center with a diagnosis of moderate to severe OSA eligible for surgery based on physical examination, respiratory polygraphy (PG) and drug induced sleep endoscopy (DISE) will be screened for eligibility. Inclusion criteria include [1]: age of at least 18 years or older [2]; ability to understand and comply with the protocol requirements, and provide written informed consent [3]; AHI of equal to or more than 15 on PG [4]; physical examination showing lingual tonsils classified as Friedman grade 3 or 4; and [5] DISE demonstrating collapse at BOT level classified as grade 2. Exclusion criteria include [1]: body mass index higher than 32 [2]; concentric collapse during DISE [3]; symptoms of Central Sleep Apnea Syndrome [4]; high co-morbidity as determined by American Society of Anaesthesiologists (ASA) score of 4 (severe systemic disease that is a constant threat to life) [5]; history of psychiatric hospitalization [6]; excessive use of opiates or benzodiazepines; and [7] previous treatment of CPAP and/or MAD or inability to tolerate MAD.

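### The primary analysis leaves out baseline AHI, which every patient has, and lets the observed data choose between a test of means and a rank test: avoidable lost precision and a shifting contrast, not an invalid analysis

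*Protocol article*

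**What the plan says.** All references are to the protocol article.

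- **Endpoint (2.5 Study outcomes):** "The primary endpoint of this study is the mean AHI measured 6 months post-intervention".
- **Baseline measurement:** the inclusion criteria in 2.2 require "AHI of equal to or more than 15 on PG", and 2.5 adds: "The PG will be performed at baseline, 6 months and 12 months".
- **Primary analysis (2.10 Statistical analysis):** independent t-test or Mann-Whitney U test, "depending on data distribution. Given the RCT design, adjustments for baseline differences are not foreseen". On how the distribution is judged: "Data normality will be assessed graphically and numerically". Secondary outcomes follow the same approach. The only adjusted analysis of the primary endpoint is a sensitivity analysis for control modality (CPAP or MAD).
- **Sample size (2.8):** 82% power with 21 per arm for a difference of 10.0, SDs 10.0 and 12.0, "with a significance level (alpha) of 0.05 using a two-sided two-sample" t-test. The same section says that "analyses will primarily focus on estimating treatment effects with 95% confidence intervals", and section 3 repeats that effect estimates and intervals come before significance.

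**The concern.** Section 2.10 makes two deliberate choices that sit badly with the aims of the trial. Neither is a gap that an unseen analysis plan would fill in, because a plan that did otherwise would contradict the article.

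First, randomisation is given as the reason not to adjust for baseline. Randomisation removes systematic imbalance. It does not remove the part of the outcome variance that baseline AHI explains, nor chance imbalance between two arms of 25. Section 3 itself names small size and type II error as limitations, so precision available from a value already collected is worth having.

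Second, the test is picked after the outcome distribution is seen, and the two tests do not address the same question. The t-test addresses the difference in mean AHI, which is the endpoint and the basis of the power calculation. Mann-Whitney addresses whether values in one arm tend to exceed those in the other, and it yields no interval for a mean difference. What the primary p-value refers to would then depend on the data.

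**Working it through.** **1. The plan's own power figure.** Inputs from 2.8: n = 21 per arm, difference 10.0, SDs 10.0 and 12.0, two-sided alpha 0.05.

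- Root-mean-square SD = √((10² + 12²)/2) = √122 = 11.05.
- SE of the difference = 11.05 × √(2/21) = 3.41.
- Noncentrality = 10/3.41 = 2.93 on 40 degrees of freedom, so power = 81.7%.

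The stated 82% reproduces.

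**2. The same trial with ANCOVA on baseline AHI.** The residual SD is 11.05 × √(1 − ρ²), with 39 degrees of freedom. The correlation ρ between baseline and 6-month AHI is not in the article, so a range is shown.

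| ρ (assumed) | Residual SD | Power, 21 per arm | 95% CI half-width (events/h) |
|---|---|---|---|
| 0 | 11.05 | 81.6% | 6.9 |
| 0.2 | 10.82 | 83.1% | 6.8 |
| 0.3 | 10.54 | 85.1% | 6.6 |
| 0.5 | 9.57 | 91.0% | 6.0 |
| 0.7 | 7.89 | 98.0% | 4.9 |

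The worst case is a loss of about 0.1 point from the lost degree of freedom. The gain is about 1.5 points at ρ = 0.2, 3 at 0.3, 9 at 0.5 and 16 at 0.7. If the SDs were those that 2.8 quotes from the earlier RCT (23.0 and 18.4, root mean square 20.8), unadjusted power for a difference of 10 would be 33%, and ANCOVA would give 36%, 42% and 57% at ρ = 0.3, 0.5 and 0.7.

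**3. How much a chance baseline gap matters.** Only the gap multiplied by the regression slope reaches the outcome. The standard error of that part at 25 per arm is ρ × 11.05 × √(2/25) = ρ × 3.12, that is 0.9/h at ρ = 0.3 and 1.6/h at ρ = 0.5. This is already inside the unadjusted SE of 3.12/h; ANCOVA removes it.

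**4. Is the switch to Mann-Whitney likely?** AHI cannot be negative. Mean minus 2 SD, from the figures in 2.8:

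- earlier RCT, conventional arm: 34.5 − 46.0 = −11.5
- earlier RCT, surgery arm: 20.8 − 36.8 = −16.0
- local TORS series, 3 months: 16.4 − 24.0 = −7.6
- local TORS series, 1 year: 10.8 − 16.96 = −6.2

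All four point to right skew. With gamma data at 16.4 (SD 12.0) in both arms and 21 per arm, Shapiro-Wilk rejects in at least one arm in 83% of simulated trials. Shapiro-Wilk at 0.05 is an assumption here; the article names no criterion.

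**5. What the switch does.** Simulated with 21 per arm; the rule is Welch unless Shapiro-Wilk rejects in either arm, then Mann-Whitney.

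- *Identical arms:* the rule rejects in about 5% of trials (4.7% with normal data, 5.6% with lognormal data, 4.6% with gamma data at 16.4/12.0).
- *True difference of 10, skewed data* (gamma, 26.4 against 16.4, SD 12): the rule rejects in about 84%, Welch in about 76%.
- *Equal means, different shapes:* TORS gamma at 16.4 (SD 12.0). The control arm is a mixture of 54% adherent with mean 5 and 46% non-adherent with mean 29.8, so its mean is 0.54 × 5 + 0.46 × 29.8 = 16.4. The 54% is the CPAP adherence figure in the Introduction; the two subgroup means are assumed. With assumed subgroup SDs of 3 and 12, the rule rejects in about 9% of trials and Welch in about 5%.

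**The case against.** The strongest defence is that the plan is sound as it stands. An unadjusted comparison is unbiased under randomisation, the trial was sized for it, and 82% is right. Declining an efficiency gain is a common choice. All of that stands.

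The gain is also uncertain. The entry limit of 15/h narrows the range of baseline AHI, and in the control arm the 6-month value may depend more on device use than on baseline severity. The mixture in step 5 shows the tension: its between-subgroup SD alone is 24.8 × √(0.54 × 0.46) = 12.4, unrelated to baseline, which fits poorly with a correlation of 0.5 to 0.7. The largest power gains and the mixture scenario should not be expected together. This stands too, and it is why the table starts at zero.

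On the test rule, a reader might infer that choosing the test from the data inflates the false-positive rate or wastes power. The simulations support neither: error stays near 5% when the arms are identical, and with skewed data the rule rejects more often than Welch under a true difference. The excess of 9% over 5% arises only when means agree and shapes differ, where Mann-Whitney's own null hypothesis is false.

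A reader might also infer that a chance gap in baseline AHI passes in full into the result. It does not; only the slope-scaled part does, and the unadjusted interval already allows for it.

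Finally, section 2.8 promises treatment effects with intervals without saying mean differences, and nothing says the mean difference would go unreported if the p-value came from Mann-Whitney. The missing normality threshold is detail that an analysis plan commonly supplies. Both are fair. What they leave untouched is that the article makes the primary test depend on the data, and that one of its two options does not test the declared endpoint.

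**Conclusion.** The point holds as a recommended improvement. The primary analysis is valid and its stated power is correct. It forgoes precision that costs one degree of freedom: between nothing and about 16 points of power over correlations from 0 to 0.7, with a range of 0.2 to 0.5 giving about 1.5 to 9 points. The article supplies no correlation, so no single figure can be claimed.

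The data-chosen test is a separate weakness. Its harm is a shifting target: the endpoint and the power calculation concern means, the article's own figures make skew likely, and the rule would then often hand the primary p-value to a test that is not about means. The size of 9% against 5% rests on an assumed adherence mixture and on Shapiro-Wilk as the criterion.

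**What to change.** In section 2.10, replace the test-choice sentence and the statement on baseline adjustment with one pre-specified primary analysis:

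- ANCOVA of 6-month AHI on treatment arm, with baseline AHI as covariate.
- Report the adjusted mean difference with a 95% CI from one named method, for example heteroscedasticity-robust standard errors, whatever the distribution looks like. Naming a single method matters; a choice between robust and bootstrap intervals would reopen the same question.
- Keep Mann-Whitney as a sensitivity analysis only.
- Use the baseline value in the same way for the continuous secondary outcomes that are compared between arms and measured at baseline, such as ODI 4% and FOSQ-35.

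The cost is a few sentences in the protocol and analysis plan. No new data, visits or patients are needed. The change should be made before 6-month outcomes are examined, because the trial is unblinded and a later choice of analysis would be hard to defend.

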After inclusion and randomization, group 1 will undergo TORS and will be hospitalized post-surgery, which is expected to be 3 days. Patient will be discharged home with pain medication and will visit the outpatient clinic after 6 weeks for evaluation of surgical wounds. Group 2 will be assessed by either a pulmonologist or a MFO surgeon. They will have an evaluation of treatment after 3 months. Time point 0 (T0) starts when patient undergoes surgery and the first day of usage of CPAP or MAD. The TORS group will complete questionnaires at 3, 6 and 12 months and will undergo PG at 6 and 12 months for evaluation of the treatment. Then, they will also have evaluation of swallowing quality of the speech language pathologist at baseline, 2 days after surgery (while hospitalized) and 6 weeks. The CPAP or MAD group will have outpatient follow-ups at the pulmonologist or MFO surgeon at the same time points. Then, they will also complete the questionnaires (3,6 and 12 months) and will undergo PG at 6 and 12 months. The CPAP will be read out at 3,6, and 12 months. For the TORS group, in addition to standards PG and quality of life questionnaires, pain scores using VAS will be recorded. The length of hospital stay will also be monitored.

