## Discussion

3

The proposed study aims to evaluate the efficacy of TORS compared with standard non-surgical therapies for OSA. By assessing both clinical effectiveness and long-term patient outcomes, this study will provide insights into the optimal OSA treatment strategy and evaluate whether surgical intervention should be positioned earlier in the treatment pathyway or remain a secondary option in clinical guidelines. Given the chronic nature of OSA, 12-month outcomes will be used to evaluate durability of treatment effects and to support interpretation beyond the primary 6-month endpoint.

A limitation of this pragmatic study design is that the control arm includes two distinct conservative modalities (CPAP and MAD), which may introduce within-arm heterogeneity. Therefore, subgroup and sensitivity analyses by control modality are planned to assess the consistency of the primary findings. Another limitation of this trial is the relatively small sample size, which may reduce statistical power to detect modest differences between groups, particularly for secondary outcomes and repeated measures analyses, increasing the risk of type II error. Therefore, results will be interpreted with emphasis on effect estimates and confidence intervals rather than statistical significance alone, and non-significant findings will be interpreted cautiously.

Importantly, outcomes of upper airway surgery depend on careful patient selection and individualized treatment planning. DISE can support this process by identifying the relevant anatomical levels and patters of collapse, enabling more targeted surgical decision-making and potentially optimizing outcomes [27,28]. In addition, while PG outcomes such as AHI remain important objective markers of disease severity, they do not fully capture treatment benefit from the patient perspective. Therefore, quality of life daytime sleepiness, and functional outcomes should be considered key endpoint when evaluating surgical versus non-surgical treatment strategies, particularly given their relevance to long-term adherence, acceptance and overall patient benefit [29].

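### The primary 6-month AHI result is an unadjusted complete-case comparison that ignores baseline and 12-month AHI, with no sensitivity analysis for missing data

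*Protocol article*

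**What the plan says.** The Statistical analysis section (2.10) fixes the primary method: "The primary outcome (AHI at 6 months) will be analysed using independent" t-test or Mann-Whitney U test, depending on the distribution. On covariates it says "Given the RCT design, adjustments for baseline differences are not foreseen". On missing values it promises only to report them with the results, and adds "Missing data will not be replaced". The sensitivity and subgroup analyses it names concern CPAP versus MAD only.

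The Sample size calculation (2.8) plans 21 evaluable patients per arm and then 25: "To correct for possible missing data, we calculated a 20% bigger sample size".

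AHI is scheduled more than once. Study outcomes (2.5) places PG at baseline, 6 and 12 months. Recruitment and screening (2.6) says of both groups that they "will undergo PG at 6 and 12 months". The Discussion mentions limited power "particularly for secondary outcomes and repeated measures analyses", but section 2.10 names no repeated-measures method.

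**The concern.** A two-group test at a single visit, with nothing imputed, uses only patients observed at that visit. A patient with a baseline and a 12-month AHI but no 6-month PG drops out of the primary comparison. Without covariates, the difference in observed means is unbiased only if, within each arm, having a 6-month PG is unrelated to the AHI it would have shown.

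That condition may fail here. The trial is open label, one arm has a single operation and the other a nightly device, and patients who abandon a device or are disappointed with surgery may be less willing to return. The authors expect enough loss to add four patients per arm. Additional patients restore numbers; they do not restore the kind of patient who is missing. At stake is the estimate and confidence interval for the primary endpoint in a 50-patient trial whose stated emphasis is on estimation.

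**Working it through.** **1. The plan's own figure.** Inputs from section 2.8: difference 10.0, SDs 10.0 and 12.0, 21 per arm, two-sided alpha 0.05.

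- SE = √((10² + 12²)/21) = √11.62 = 3.41; noncentrality = 10/3.41 = 2.93 on 40 df; power = 81.7%. The stated 82% is reproduced.
- Inflation: 21 × 1.20 = 25.2, stated as 25.

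**2. What the inflation protects.**

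- 25 falls to 21 with a loss of 4/25 = 16%.
- A 20% loss leaves 20 + 20 and power of 79.7%.
- If all 8 losses fall in the control arm (25 TORS, 17 control), power is 78.8% or 81.7%, depending on which arm has which SD.

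Power is thus robust even to lopsided loss. None of these calculations touches bias.

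**3. Bias of the complete-case difference.** Let m be the fraction missing in an arm and g the mean AHI of missing minus observed patients in that arm. The full-arm mean is the observed mean + m·g. For control minus TORS, with C for control and T for TORS:

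bias = −(m_C·g_C − m_T·g_T)

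The article gives neither m by arm nor g. Assume g = 5 to 15 events/h in both arms (missing patients worse):

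| Loss TORS / control | Bias, g = 5 | Bias, g = 15 |
|---|---|---|
| 16% / 16% | 0 | 0 |
| 8% / 24% | −0.8 | −2.4 |
| 4% / 32% | −1.4 | −4.2 |

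Against the design difference of 10.0 this is 0% to 42%. The sign reverses if missing patients are better than observed ones, or if losses fall mainly in the TORS arm.

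**4. Simulation of baseline-dependent loss.** Plan inputs: 25 per arm, means 34 (control) and 24 (TORS), SDs 10 and 12. Assumptions: correlation 0.5 between baseline and 6-month AHI; TORS loss 20% at random; control loss with logit −1.6 ∓ 1.0 × standardised baseline AHI, about 21% overall. 4,000 trials each; true difference 10.

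| Controls lost | Complete-case, unadjusted | Complete-case, baseline-adjusted |
|---|---|---|
| Mainly low baseline AHI | 10.9 (SE 3.47) | 9.9 (SE 3.06) |
| Mainly high baseline AHI | 9.1 | 10.1 |

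The unadjusted bias is about 1 event/h in either direction, roughly a quarter of one SE, and baseline adjustment removes nearly all of it.

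**5. Where the precision gain comes from.** With 20 per arm and no informative loss, the unadjusted SE is √(100/20 + 144/20) = 3.49. Baseline adjustment multiplies it by √(1 − 0.5²) = 0.866, giving 3.02 (3.52 and 3.10 in simulation). The gain therefore comes from adjusting for baseline, not from handling missing data. In step 4 the variance ratio is (3.06/3.47)² = 0.78, a reduction of about 22%.

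**The case against.** The strongest reply is that nothing shows the rule does harm here. Complete-case analysis is valid if loss is unrelated to outcome within arm. The 6-month PG is scheduled in both arms whatever the adherence, so a patient who stops the device can still be measured. The simulated bias is small, and plain ANCOVA on complete cases produced both the correction and the precision gain without replacing any value. All of that stands. It limits the size of the point but does not answer the absence of both baseline adjustment and any check on missing data.

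Several stronger readings are tempting but not supported:

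- **That loss will differ by arm.** The Introduction's 30% CPAP refusal and 54% adherence at 3 months describe refusal and use, not missed PGs. Differential loss is an inference.
- **That half the design effect could be lost.** If 20% of controls stop, stay at 34 and miss the PG while the others average 10, the full control mean is 0.8 × 10 + 0.2 × 34 = 14.8, a shift of 4.8. But the treated mean of 10 is an assumption, whereas section 2.8 plans 34 for the control group. The shift depends on unobserved AHI, so a model assuming missing at random would not repair it either if those patients also lack a 12-month PG and stopping is unrelated to baseline.
- **That the no-replacement rule contradicts intention-to-treat.** The conflict in section 2.10 lies in the analysis set, which takes everyone "except those with major protocol violations, no post-baseline data, or no study intervention". That is a separate matter.
- **That the 20% enlargement contradicts the rule.** It is the usual way to protect the power of a complete-case analysis.
- **That every secondary outcome needs the same model.** Section 2.8 already labels secondary outcomes exploratory.

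**Conclusion.** The point holds in a moderate form and should be acted on. The article itself fixes the method, so this is not detail left to an unseen analysis plan: the primary result is an unadjusted complete-case comparison that makes no use of baseline or 12-month AHI and has no sensitivity analysis for missing values. The size and sign of any bias cannot be derived from the article. It is about 1 event/h either way under the assumptions of step 4, and between 0 and 4.2 events/h under the wider assumptions of step 3. The reduction in SE from about 3.5 to 3.1 rests on the assumed correlation of 0.5 and is a benefit of baseline adjustment alone. The Discussion's mention of repeated-measures analyses is a loose end to reconcile with section 2.10, not evidence of a faulty primary test.

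**What to change.** In section 2.10, take the primary 6-month contrast from a likelihood mixed model of AHI at 6 and 12 months with arm, visit, arm-by-visit and baseline AHI, reported with its 95% confidence interval. Include every randomised patient with at least one follow-up AHI, in the allocated arm. With complete data this is essentially ANCOVA. A patient with no follow-up PG contributes nothing to it.

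Because the model assumes missing at random and does not correct loss that depends on the unobserved AHI, prespecify one sensitivity analysis: set a missing 6-month AHI to the patient's baseline AHI, or apply a delta adjustment by arm. Report the number missing and the reasons by arm. Align the Discussion's reference to repeated measures with this text.

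The cost is revised wording and a little more analysis work, with no new patients or visits. The downside is reliance on missing at random, which the sensitivity analysis probes.
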